## Abstract

**Background:**

Amnestic mild cognitive impairment (aMCI), a common neurodegenerative disease affecting older adults, has garnered significant research interest over the past few years. While previous studies have suggested that acupuncture holds promise as a clinical intervention to improve cognitive function in patients with aMCI, the long-term effect of acupuncture treatment for aMCI remains unclear.

**Methods:**

This is a multicenter, single-blinded, randomized controlled trial (RCT) with a long-term follow-up.166 patients diagnosed with aMCI will be randomly divided into acupuncture group (AG) and sham acupuncture group (SA). The intervention will last for 12 weeks (2 sessions per week), follow-up for 48 weeks, and the study will last a total of 60 weeks. The primary outcomes are the changes in the Alzheimer’s Disease Assessment Scale-Cognitive (ADAS-Cog) score from baseline to week 12 and from baseline to week 60. Generalized estimating equations (GEE) will be used to assess the impact of the acupuncture intervention on outcome variables over time at baseline and weeks 12, 24, 48, and 60.

**Discussion:**

This protocol outlines a detailed procedure for a multicenter RCT designed to further evaluate the long-term effect of acupuncture in managing aMCI. We anticipate that the findings of this research will provide valuable insights and evidence-based recommendations for the clinical management of this patient population.

**Trial registration:**

The trial was registered at Chinese Clinical Trial Registry on 28 May 2024 (Number: ChiCTR2400084932).

## Introduction

Amnestic mild cognitive impairment (aMCI) is a common neurodegenerative disease affecting older adults and is also the most prevalent subtype of mild cognitive impairment (MCI), accounting for approximately two-thirds of all cases. The hallmark clinical features include memory decline and impaired cognitive function, while individuals generally maintain their ability to perform daily activities. A meta-analysis study from 2022 showed that the prevalence rate of MCI in people over 50 years old was 15.56% globally, of which the prevalence rate of aMCI was 10.03% [1]. Moreover, the prevalence rate increased with age. A report released by the World Health Organization in 2019 showed that Alzheimer’s disease (AD) and other types of dementia have become the seventh leading cause of death [1]. However, the pathogenesis of AD is complex and the therapeutic effect is general [2]. aMCI represents a transitional state between AD and normal aging [3–5], and its risk of progression to AD is about 40% [6]. Given that aMCI is the early stage of AD and the large number of patients, early intervention of aMCI is particularly necessary [7].

However, the pathogenesis of aMCI remains elusive. While it shares some pathophysiological mechanisms with AD, there are numerous hypotheses regarding its origins [8–13]. Currently, there are no approved drugs that effectively manage aMCI and improve cognitive function [14]. Studies have demonstrated that existing medications are not only ineffective in controlling aMCI [15,16] but also frequently cause adverse reactions like nausea, diarrhea, and vomiting [17]. Concerningly, projections indicate that by 2050, the annual cost of treating cognitive impairment in China alone will reach 1.89 trillion yuan, with the global cost reaching an astounding USD 9.12 trillion [18]. This underscores the severe economic burden that aMCI places on individuals, families, and society. Given that aMCI is a potential precursor to AD, the development of safe, effective, and affordable treatments is of paramount importance.

Acupuncture, a commonly used and well-tolerated complementary and alternative therapy, has experienced a steady rise in popularity for treating aMCI [19]. Evidence-based research suggests that it is an effective clinical approach for improving cognitive function in aMCI patients [20–22]. We have completed a preliminary clinical trial on acupuncture intervention in aMCI patients [23], demonstrating lasting but unclearly sustained positive effects. Acupuncture is a complex intervention [24], and the placebo effect of acupuncture is controversial [25–27]. We will introduce the sham acupuncture group in the control arm. This ensures comparable credibility to true acupuncture while minimizing actual stimulation [25]. Additionally, aMCI is a chronic disease, and its impact on health and life is long-standing. We believe an extended follow-up is necessary to elucidate the long-term efficacy. To further solidify our findings and establish generalizability, we propose conducting a large-scale, sham-acupuncture controlled, long-term follow-up clinical trial.

### Objective

(1) To evaluate the efficacy and safety of acupuncture compared to sham acupuncture in the treatment of patients with aMCI; (2) To determine the long-term effect of acupuncture in the treatment of aMCI patients.

## Methods

This study employs a randomized controlled trial design. The protocol adheres to the Standard Protocol Items: Recommendations for Interventional Trials (SPIRIT) [28] (S1 File). This study is registered in the Chinese Clinical Trials Register (ChiCTR2400084932) and will be conducted in strict compliance with the Declaration of Helsinki. It has received approval from the Medical Ethics Committee of Hospital of Chengdu University of Traditional Chinese Medicine (ethical approval number: 2023KL-144). The study recruitment began on June 30, 2024 and is scheduled to conclude in December 2026. Data collection will end in March 2027, and data analysis will be completed in June 2027.

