### Study design

This prospective, multicenter randomized controlled trial (RCT) will employ a 1:1 allocation ratio with concealed allocation to assign 166 patients with aMCI evenly into either the acupuncture group (AG) or sham acupuncture group (SA) randomly. The intervention will last for 12 weeks (2 sessions per week), followed by a 48-week follow-up period, for a total observation period of 60 weeks.

The trial will be conducted across the outpatient clinics of nine hospitals in China (the West China Hospital, the Fourth People’s Hospital of Chengdu, the Sichuan Province People’s Hospital, Traditional Chinese Medicine Hospital of Pidu district, the Nanchong Second People’s Hospital, Traditional Chinese Medicine Hospital of Meishan, Chengdu First People’s Hospital, the Rehabilitation Hospital of Sichuan Province and Hospital of Chengdu University of Traditional Chinese Medicine). Recruitment will involve social media advertisements and postings at community centers. Research assistants will obtain written informed consent from willing participants before baseline assessment, and data collectors will remain blinded to group assignments. Figs 1–3 illustrate the research procedure and results evaluation schedule.

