### Sample size

The Alzheimer’s Disease Assessment Scale-Cognitive (ADAS-Cog) score will serve as the primary index to evaluate cognitive function improvement in patients with MCI. The sample size calculation for this trial was based on our previous study [30] and pilot study, we anticipate an average effect of 3.5 in the acupuncture group and 1.5 in the control group, with a standard deviation of 3.5 between the groups. Using PASS software, we calculated a required sample size of 132 subjects (α = 0.05, 1 − β = 0.90, two-sided). To account for a potential 20% loss to follow-up, we plan to enroll 83 patients in each group, for a total of 166 aMCI patients in the study.

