### Outcomes

#### Primary outcome measures.

Cognitive function will be measured using the ADAS-Cog scale [35]. The primary outcomes will be the changes in the ADAS-Cog score from baseline to week 12 and from baseline to week 60. The ADAS-Cog, comprised of 12 tasks, evaluates various aspects of cognition, including memory, language, praxis (ability to perform actions), orientation, and attention. It is a widely used instrument in dementia research, with lower scores indicating less cognitive impairment.

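### The stated calendar closes data collection about three months after recruitment ends, so patients enrolled after early February 2026 (about a third under even accrual) cannot reach the week-60 primary outcome

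*Protocol article*

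**What the plan says.** Three places in the protocol article bear on this.

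- **Methods, opening paragraph**, on the calendar: "The study recruitment began on June 30, 2024 and is scheduled to conclude in December 2026. Data collection will end in March 2027". The analysis is to be finished in June 2027.
- **Study design**, on time per patient: 12 weeks of treatment "followed by a 48-week follow-up period, for a total observation period of 60 weeks".
- **Primary outcome measures**: "The primary outcomes will be the changes in the ADAS-Cog score from baseline to week 12 and from baseline to week 60".

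Nothing in the article shortens follow-up for late recruits, describes administrative censoring, or gives the week-60 visits a separate closing date.

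**The concern.** Data collection has to stay open for at least 60 weeks after the last enrolment if every patient is to have the week-60 assessment. The stated calendar leaves roughly the length of the treatment course. The dates therefore contradict the 60-week schedule and one of the two primary outcomes.

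The long-term effect is the trial's second objective and the reason given for extending follow-up. If the dates were followed, that question would rest on the earlier recruits, with multiple imputation filling in an outcome that later recruits never had the chance to provide. The week-12 outcome would hardly be touched, so the loss falls on the part of the trial that is meant to be new.

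**Working it through.** **Inputs**

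| Quantity | Value | Source |
|---|---|---|
| Recruitment | 30 June 2024 to December 2026 (day not given) | Methods, opening paragraph |
| End of data collection | March 2027 (day not given) | Methods, opening paragraph |
| Observation per patient | 12 + 48 = 60 weeks = 420 days | Study design |
| Planned difference | 3.5 − 1.5 = 2.0 points | Sample size: "we anticipate an average effect of 3.5 in the acupuncture group and 1.5 in the control group" |
| SD | 3.5 | Sample size: "with a standard deviation of 3.5 between the groups" |
| Error rates | two-sided α 0.05, power 0.90 | Sample size: "α = 0.05, 1 − β = 0.90, two-sided" |
| Evaluable / enrolled | 132 / 166, with 20% loss | Sample size |
| Accrual pattern | even over the window | **Assumption**; no rate is stated |

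**1. Reproducing the plan's sample size.** The normal approximation gives n per arm = 2 × (1.960 + 1.282)² × (3.5/2)² = 64.4, so 65. The exact t-test gives power 0.8985 at 65 per arm and 0.903 at 66. Hence 66 per arm, 132 in total. Allowing for loss, 66 / 0.8 = 82.5, so 83 per arm and 166 in total. The stated figures reproduce and are not in dispute.

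**2. Gap between the two closing dates.** From 31 December 2026 to 1 March 2027 is 60 days (8.6 weeks). From 1 December 2026 to 31 March 2027 is 120 days (17.1 weeks). The design needs 60 weeks, so no choice of days within the stated months closes the gap.

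**3. When the last patient reaches week 60.** 1 December 2026 + 420 days = 25 January 2028. 31 December 2026 + 420 days = 24 February 2028. The second date is 330 days, about 11 months, after 31 March 2027.

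**4. Last enrolment that can reach week 60.** 31 March 2027 − 420 days = 4 February 2026. 1 March 2027 − 420 days = 5 January 2026. The February date is the more lenient reading.

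**5. Share affected under even accrual.** Share = (recruitment end − cutoff) / (recruitment end − 30 June 2024). Patients reaching week 60 = 166 × (1 − share), then × 0.8 for the plan's own loss. Power uses the normal approximation Φ(2 / (3.5 × √(2/m)) − 1.96), with m the number per arm.

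| Collection ends | Recruitment ends | Days late / window | Share | Patients late | Can reach week 60 | After 20% loss | Power, no other loss | Power, 20% loss |
|---|---|---|---|---|---|---|---|---|
| 31 Mar 2027 | 1 Dec 2026 | 300 / 884 | 33.9% | 56.3 | 109.7 | 87.7 | 0.849 | 0.763 |
| 31 Mar 2027 | 31 Dec 2026 | 330 / 914 | 36.1% | 59.9 | 106.1 | 84.9 | 0.837 | 0.749 |
| 1 Mar 2027 | 1 Dec 2026 | 330 / 884 | 37.3% | 62.0 | 104.0 | 83.2 | 0.830 | 0.741 |
| 1 Mar 2027 | 31 Dec 2026 | 360 / 914 | 39.4% | 65.4 | 100.6 | 80.5 | 0.818 | 0.727 |

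For comparison, the same approximation gives 0.907 at 66 per arm. An exact t-test at 85 patients gives 0.739, where the approximation gives 0.749.

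**6. Week 12.** If collection closes on 31 March 2027, every patient can reach week 12. If it closes on 1 March 2027, the cutoff is 7 December 2026, and at most 24 / 914 = 2.6% of patients are affected.

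**The case against.** The strongest counter-argument is that one year may simply be misprinted. Had recruitment been meant to end in December 2025, a patient enrolled on 31 December 2025 would reach week 60 on 24 February 2027, and the other two dates would fit the design. That is plausible, but the document cannot settle it. The sentence is explicitly about recruitment, and the text as it stands would still be wrong. It does mean that December 2026 should not be taken as the reliable date and March 2027 as the faulty one.

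The objections to the size of the problem have some force:

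- The share of one third depends on even accrual. Faster early recruitment makes it smaller, and slower early recruitment makes it larger.
- The Sample size section does not tie its 2-point difference to week 60, so 90% power at that visit is an inference from week 60 being a primary time point.
- The power figures are for a two-group comparison of patients observed at week 60. The planned GEE, with baseline and the intermediate visits, may recover some precision. Without the extra 20% loss the figure is 0.82 to 0.85.
- Missingness fixed by enrolment date is plausibly unrelated to outcome, so the missing-at-random assumption is reasonable for it. The likely harm is lost information more than bias. Imputation, however, does not create the week-60 measurements that were never taken.

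These points make the numerical consequences conditional. They leave the contradiction in the dates intact.

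**Conclusion.** The concern holds. The calendar allows 8.6 to 17.1 weeks after the end of recruitment where the design requires 60. This follows from the article's own dates and needs no assumption.

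The consequences assume that the dates are followed and that accrual is even. On that basis, about 56 to 65 of 166 patients could not supply the week-60 primary outcome, and 80 to 88 evaluable patients would remain against 132 required. Power in a simple comparison would be about 0.73 to 0.76. Week 12 is essentially unaffected. Because a primary outcome and the trial's long-term objective are at stake, the dates must be corrected.

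**What to change.** Make the calendar follow from the design, in one of two ways according to which date is firm:

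- **If recruitment does run to December 2026:** set the end of data collection to last enrolment plus 60 weeks. That is 24 February 2028 for a last enrolment on 31 December 2026, plus any visit window. Keep the present interval of about three months to completion of the analysis.
- **If March 2027 is firm:** correct the end of recruitment to 4 February 2026 at the latest, or 5 January 2026 if collection closes on 1 March.

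In either case, add a sentence saying that the week-60 analysis is run only after the last week-60 visit and database lock.

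The cost is a correction of dates in the article and wherever else the same dates appear, such as the registry entry and the ethics file. The first option adds about 11 calendar months of follow-up, but no visit beyond those already promised to each patient. If the recruitment year is a misprint, the second option is a one-line correction with no loss of data. If recruitment is in fact still needed after the cutoff, the second option would mean enrolling fewer than 166, and the first is then the one that preserves the planned sample.

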### Study design

This prospective, multicenter randomized controlled trial (RCT) will employ a 1:1 allocation ratio with concealed allocation to assign 166 patients with aMCI evenly into either the acupuncture group (AG) or sham acupuncture group (SA) randomly. The intervention will last for 12 weeks (2 sessions per week), followed by a 48-week follow-up period, for a total observation period of 60 weeks.

The trial will be conducted across the outpatient clinics of nine hospitals in China (the West China Hospital, the Fourth People’s Hospital of Chengdu, the Sichuan Province People’s Hospital, Traditional Chinese Medicine Hospital of Pidu district, the Nanchong Second People’s Hospital, Traditional Chinese Medicine Hospital of Meishan, Chengdu First People’s Hospital, the Rehabilitation Hospital of Sichuan Province and Hospital of Chengdu University of Traditional Chinese Medicine). Recruitment will involve social media advertisements and postings at community centers. Research assistants will obtain written informed consent from willing participants before baseline assessment, and data collectors will remain blinded to group assignments. Figs 1–3 illustrate the research procedure and results evaluation schedule.

**Fig 1 pone.0346717.g001:**
[figure not shown]
A flow chart of the trial.

**Fig 2 pone.0346717.g002:**
[figure not shown]
CONSORT 2010 flow diagram.

**Fig 3 pone.0346717.g003:**
[figure not shown]
SPIRIT schedule.

### Eligibility criteria

#### Inclusion criteria.

Patients who meet 8 following criteria will be included: (1) a diagnosis of aMCI according to the Jak/Bondi 2014 criteria [29]; (2) age between 50 and 80 years, regardless of sex; (3) a disease course≥ 3 months; (4) a Clinical Dementia Rating (CDR) score of 0.5; (5) a Hachinski Ischemic Score (HIS)≤4; (6) ≥8 years of education (including vocational) with the ability to understand and complete scales; (7) willingness to participate and provide signed informed consent; (8) no contraindications for magnetic resonance imaging (MRI) scanning.

#### Exclusion criteria.

Patients will be excluded if they meet any of the following criteria: (1) receiving treatment that interferes with cognitive function (e.g., the treatment of acute psychotic illness, such as donepezil, memantine, oxiracetam, sodium oligomannate capsules, and rivastigmine); (2) a history of neurological conditions affecting cognitive function confirmed by examination, except in patients with suspected early AD (including vascular dementia, Parkinson’s disease, traumatic brain injury, brain tumor or other diseases which might lead to neurological injury and abnormal brain structure). Presence of systemic diseases that could cause cognitive decline (such as hepatic encephalopathy, Hashimoto’s encephalopathy, metabolic encephalopathy, renal encephalopathy, and anemia); (3) the brain MRI showing infection or other local lesions, infarction in vital memory brain areas, multiple embolic infarctions, or severe white matter lesions (Fazekas score≥3); (4) a history of psychiatric illness (e.g., bipolar disorder, schizophrenia), severe anxiety (Hamilton anxiety [HAMA] scale score≥29), major depression (Hamilton Depression [HAMD] scale score≥24), or tumor; (5) severe skin infection, hemorrhagic disease, or bleeding tendency; (6) severe drug dependence, drug, smoking, or alcohol abuse; (7) pregnant, potentially pregnant, or lactating females; and (8) receipt of any acupuncture treatment or participation in other clinical trials within 6 months before enrollment.

#### Withdrawal criteria.

Patients will be informed that they can withdraw from the study at any time. However, the researchers will ask for and record the reason for withdrawal. Patients will be withdrawn when the following conditions occur: (1) patients who do not meet the inclusion criteria and were mistakenly enrolled; (2) patients who utilize prohibited treatments or independently modify their treatment plan as outlined in the protocol; (3) patients who experience significant life events or circumstances that make continued participation unsuitable for their well-being.

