### Safety measurements

Throughout the intervention period, patients will be closely monitored for adverse events (AEs). This includes routine physical examinations and vital sign monitoring for all participants. The research team will implement all necessary measures to prevent potential accidental injuries associated with the study. Should any such injuries occur, the project will cover the related medical expenses. Comprehensive documentation will be maintained for any AEs, including immediate provision of appropriate medical care to affected individuals and a thorough investigation to determine the cause of the events. As acupuncture can potentially cause AEs like bleeding, hematoma, fainting, severe pain, or local infection [39], any serious event will be promptly reported to the ethics committee, and the affected participant will be withdrawn from the study.

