### Statistical analysis

The data will be processed and analyzed by an independent statistician using IBM SPSS 26.0. An Intention-to-Treat (ITT) analysis approach will be adopted. Sensitivity analysis will use the Per-protocol (PP) analysis method. A two-sided *P-value* < 0.05 will indicate statistical significance. Descriptive statistics for continuous variables will include means and standard deviations (for normally distributed data) or medians and interquartile ranges (otherwise). Categorical variables will be presented as frequencies and percentages. Generalized estimating equations (GEE) will be used to assess the impact of the acupuncture intervention on outcome variables over time at baseline and weeks 12, 24, 48, and 60, with baseline measurement, time, group, and the group-by-time interaction included as covariates, as these factors may influence the efficacy of the acupuncture intervention. Patterns of missingness will be examined, and multiple imputation will be used assuming missing at random, with sensitivity analyses conducted where appropriate.

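### The mandatory withdrawal rules do not separate stopping study treatment from ending assessment, so week-60 scores that the ITT analysis needs may never be collected

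*Protocol article*

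**What the plan says.** The Withdrawal criteria section of the protocol article first tells patients that they may leave the study whenever they wish. It then turns mandatory: "Patients will be withdrawn when the following conditions occur". Three grounds follow:

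- "patients who do not meet the inclusion criteria and were mistakenly enrolled";
- "patients who utilize prohibited treatments or independently modify their treatment plan as outlined in the protocol";
- major life events or circumstances that make continuing unsuitable for the patient's well-being.

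Safety measurements adds a fourth: "any serious event will be promptly reported to the ethics committee, and the affected participant will be withdrawn from the study".

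Statistical analysis says "An Intention-to-Treat (ITT) analysis approach will be adopted" and, for missing data, "multiple imputation will be used assuming missing at random". Per-protocol is the only sensitivity analysis named. Others are promised where appropriate, without detail.

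Primary outcome measures sets two primary outcomes, ADAS-Cog change to week 12 and to week 60. Study design gives 12 weeks of treatment and 48 weeks of follow-up. Secondary outcome measures schedules ADAS-Cog at weeks 12, 24, 36, 48 and 60.

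**The concern.** An ITT comparison needs outcomes from every randomised patient, whatever treatment was taken and whatever rule was broken. The withdrawal rules end participation for some of exactly those patients, and the article does not distinguish the end of needling from the end of assessment. Treatment occupies 12 of the 60 weeks. In the other 48 there is no study treatment left to stop, so a withdrawal in that period mainly costs outcome data.

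The reason for removal also matters. A patient who declines during follow-up may be started on a drug for cognition and then be withdrawn for it. The missing week-60 score may then depend on a decline that no visit recorded. The second stated objective is the long-term effect, so the week-60 comparison is where this would do most harm. Scores that were not collected cannot be recovered by any later analysis plan.

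**Working it through.** **1. The plan's own figure.** Inputs from Sample size: mean effects 3.5 and 1.5 (difference 2.0), SD 3.5, two-sided alpha 0.05, power 0.90, 20% loss.

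- Normal approximation: n per arm = 2 × (1.960 + 1.282)² × 3.5² / 2.0² = 64.4, rounded up to 65 (130 in total).
- Two-sample t-test: 65.33, rounded up to 66 per arm, 132 in total. This matches the plan.
- Allowance for loss: 66 / 0.80 = 82.5, rounded up to 83 per arm, 166 in total. This matches too.

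The sample size is not in dispute.

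**2. The passages side by side.**

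| Ground | Wording on leaving | Likely link to cognitive decline |
|---|---|---|
| Enrolled in error | withdrawn | none; fixed at baseline |
| Prohibited treatment | withdrawn | plausible, if the treatment is a drug for cognition |
| Self-modified plan | withdrawn | uncertain |
| Serious event | withdrawn from the study | uncertain; the examples given are needling harms |

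The article has no list of prohibited treatments. The link to cognitive drugs is inferred from exclusion criterion 1, "receiving treatment that interferes with cognitive function", whose examples include donepezil, memantine and rivastigmine.

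**3. Bias under missing at random.** Let pA and pS be the shares removed in the acupuncture and sham arms. Let D be the number of ADAS-Cog points by which removed patients truly do worse than imputed, taken as equal in both arms. Each arm's estimated improvement is then too favourable by p × D, so

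estimated benefit − true benefit = D × pA − D × pS = −D × (pS − pA).

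All values of pA, pS and D below are assumptions; the article gives none.

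| pA | pS | D | Estimate minus truth | Share of planned 2.0 |
|---|---|---|---|---|
| 5% | 10% | 2 | −0.10 | 5% |
| 10% | 20% | 2 | −0.20 | 10% |
| 10% | 20% | 5 | −0.50 | 25% |
| 10% | 20% | 6 | −0.60 | 30% |
| 10% | 10% | any | 0 | 0% |
| 15% | 10% | 5 | +0.25 | 12.5% |

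If more sham patients are removed, the benefit is understated. If more acupuncture patients are removed, it is overstated. Equal removal and equal prognosis give no bias.

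**4. Power, as a side check.** Difference 2.0, SD 3.5, t-test:

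| Missing at week 60 | Patients per arm | Power |
|---|---|---|
| 0% | 83 | 0.955 |
| 20% (planned) | 66.4 | 0.905 |
| 25% (assumed) | 62.2 | 0.885 |
| 30% (assumed) | 58.1 | 0.863 |

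Even if removals by rule came on top of the planned 20%, an extra 5 to 10 percentage points would cost little power.

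**The case against.** Several stronger readings are tempting, and the text does not carry them.

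- **That the rules flatly contradict ITT, or amount to excluding patients after randomisation.** Nothing says that withdrawn patients leave the ITT set, and multiple imputation can keep them in their randomised arm. The conflict is with the purpose of ITT, because their later scores would be modelled, not observed.
- **That later outcomes are certainly not collected.** The mandatory clause in Withdrawal criteria says only that patients are withdrawn, and the full protocol may provide for follow-up. However, that section opens with leaving the study, Safety measurements names the study outright, and the article states no continued assessment.
- **That missing at random is false by construction.** It allows missingness to depend on recorded scores, and ADAS-Cog is measured at five visits after baseline. Decline that prompts a new drug may already show there. The assumption is doubtful, not refuted.
- **That all these patients are removed for doing badly.** As the table of grounds shows, this fits the prohibited-treatment ground best and does not fit enrolment in error. The serious-event rule stands in a paragraph that opens with the intervention period, so its reach over all 60 weeks is unclear.
- **That the roughly 40% risk of progression to AD in the Introduction shows such removals are common.** That figure has no time horizon, and progression is not a withdrawal ground.
- **That the 20% allowance leaves out removals by rule.** Sample size does not say so either way.

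The choice of a particular missing-data sensitivity analysis may also be left to an analysis plan that is not shown. That is fair, but no analysis plan can supply scores that were not collected. Per-protocol typically drops the same patients, so it does not test the missing-at-random assumption.

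**Conclusion.** The concern holds in a limited form and should be fixed. Followed as written, the rules in Withdrawal criteria and Safety measurements create avoidable missing ADAS-Cog data, especially at week 60, and undercut the ITT analysis without formally contradicting it. For patients who start a cognition-affecting drug, missing at random is doubtful; that link is itself an inference.

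The size and sign of any bias cannot be known from the article. The range of 0.1 to 0.6 points (5 to 30% of the planned difference) rests entirely on assumed removal shares and an assumed 2 to 6 point gap. A reader might infer that the rules favour acupuncture. In the scenario that comes first to mind, more decline and removal under sham, they would understate its benefit. Bias is the main issue and loss of power is minor.

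**What to change.** Reconcile Withdrawal criteria and Safety measurements with Statistical analysis, leaving all decisions on stopping treatment to the clinicians:

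1. State separately when study treatment ends and when outcome assessment ends.
2. Keep patients who stop or change study treatment, or were enrolled in error, on the scheduled assessments to week 60, unless they withdraw consent or continued participation is judged unsuitable for their well-being. That last ground is already in the plan and should stay.
3. Say explicitly whether patients with a serious event continue to be assessed, under the same two exceptions.
4. Record the date and reason of each such event.
5. Include every collected score in the ITT analysis.
6. Add a delta-adjusted sensitivity analysis for scores still missing at week 60.

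The cost is a protocol amendment, notice to the nine hospitals, and some extra effort to retain patients who have stopped treatment. The assessments are already scheduled and the sample size of 166 does not change. Recruitment is planned to run to December 2026 and data collection to March 2027, so an early amendment saves the most data.
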